### Patient recruitment

LBP patients who fulfil the inclusion criteria, will be screened by a Physiotherapist and Orthopaedic specialist and will be invited to participate in this study. Inclusion criteria will be as follows: has experienced an episode of LBP of more than four weeks’ duration with a score on the visual analogue scale (VAS) of at least 4, is aged between 20 and 40 years old and has a body mass index (BMI) of between 18.5 kg/m^2^ and 29.9 kg/m^2^. The patients will be excluded if they suffer from identified health problems such as nerve involvement or compression, spinal disorders (e.g., spondylolisthesis, herniated nucleus pulposus, spondylosis, spinal fracture, back surgery), neurological deficit (e.g., multiple sclerosis, hemi/ para-paresis or myelopathy), and infectious diseases (e.g., AIDS or tuberculosis). Smokers and those experiencing menstruation, pregnancy or febrile convulsion during the study will also be excluded. LBP patients who are taking medication containing analgesics or steroids, and those who have sought treatment for LBP in the past two weeks will also be excluded.

An explanatory statement will be given to those deemed to be eligible to participate, and written informed consent will be obtained before the commencement of the study. Consenting participants will then be randomly assigned into the two groups as described above.

### Intervention

The patients in the TMM group will be treated by one certified practitioner of TMM, with the treatment being applied for 30 min in one session only on the area of pain in the lower back. The practitioner will follow the protocol of TMM that has been provided for and approved by the Ministry of Health, Malaysia [18]. The massage techniques involved in TMM are fan stroking, basic kneading, thumb stroking, and static pressure (Fig. 1). On the other hand, the patients in the control group will undergo a relaxation position for 30 min (Fig. 1).

**Fig. 1 Fig1:**
[figure not shown]
Study protocol

### Outcome measures

The primary outcome measure for this study is the difference in the level of SP in blood and saliva samples pre- and post-intervention. All samples will be analysed at the Collaborative Drug Discovery Research (CDDR) Laboratory, Faculty of Pharmacy, UiTM Puncak Alam Campus.

The secondary outcome measures include the levels of inflammatory mediators [i.e., TNF-α, IL-1β, IL-8, monocyte chemotactic protein-1 (MCP-1), IL-6 and IL-10, and the soluble form of intercellular adhesion molecule (sICAM-1)] in both blood and saliva samples [20]. Other secondary outcome measures also include the visual analogous scale (VAS) score (indicating the pain intensity) and the Roland-Morris Disability Questionnaire (RMDQ) [21] score (assessing the level of disability associated with LBP).

### Instruments

Both blood and saliva samples will be collected and centrifuged (10,000 g and 4 °C for 15 min) to eliminate debris and cellular matter. Then, the Human Substance P EIA kit (Cusabio Biotech; CSB-E08357h) will be used to determine the level of SP. Other inflammatory mediators, such as TNF-α (eBioscience; BMS2034TEN), IL-1β (Cayman chemical;583311-96 well), IL-6 (BMS213/2TEN), IL-8 (eBioscience; BMS204/3), IL-10 (eBioscience; BMS215/2), monocyte chemotactic protein-1(MCP-1) (eBioscience; BMS281) and the soluble form of the intercellular adhesion molecule (sICAM-1) (Arigo; ARG80215), will be tested individually in both blood and saliva samples using a human Elisa kit (Table 1).

**Table 1 Tab1:** Analytical and assessment characteristics

No.	Assessment	Explanation
1.	Blood sample	Blood collection
		- 10 ml of venous blood will be taken by a trained nurse.
		- The whole blood will be collected into a plain polyethylene tube until blood clot formation.
		- The clots will be separated from the wall of tube using a wooden applicator stick.
		- The serum will be separated by centrifugation at 10,000 g at 4 °C for 15 min to eliminate debris and cellular matter.
		Blood test
		1) Substance P
		- The blood serum will be tested using Human Substance P EIA kit (Cusabio Biotech)
		2) Cytokines
		- The blood serum will be tested individually using Elisa kits to investigate
		a) TNF-α
		b) IL-1β
		c) IL-6
		d) IL-8
		e) IL-10
		c) monocyte chemotactic protein-1 (MCP-1)
		d) The soluble form of intercellular adhesion molecule (Sicam-1).
2.	Saliva sample	Saliva collection
		- 3 to 4 ml of unstimulated (resting) whole saliva will be collected 2 min after the patient has rinsed his/hermouth several times with tap water.
		- The accumulated saliva in the floor of the mouth will be drawn by a plastic disposable pipette and collected into a plastic polyethylene tube.
		- The collected saliva will be centrifuged at 10,000 g at 4 °C for 15 min to eliminate debris and cellular matter.
		Blood test
		1) Substance P
		- The blood serum will be tested using Human Substance P EIA kit (Cusabio Biotech)
		2) Cytokines
		- The blood serum will be tested individually using Elisa kits to investigate:
		a) TNF-α
		b) IL-1β
		c) IL-6
		d) IL-8
		e) IL-10
		c) monocyte chemotactic protein-1 (MCP-1)
		d) The soluble form of intercellular adhesion molecule (sICAM-1).
3.	Visual Analogue Scale (VAS)	- Pain intensity will be measured using VAS by asking the patients to describe their pain level before and after treatment.
4.	Roland-Morris Disability questionnaire	- Functional disability will be measured using the Roland-Morris Disability questionnaire.

The VAS is a measurement of pain intensity and has been proven to be reliable and valid [22, 23]. The VAS scale ranges from ‘0’ to ‘10’ with a different facial expression whereby 0 represents ‘no pain’ and 10 represents the ‘worst possible pain’. Patients will be asked to rate their pain level using the VAS pre- and post- intervention.

The RMDQ is an instrument for assessing the level of disability associated with LBP [21]. RMDQ contains 24 items which relate to several activities in daily life. The scoring depends on the patient’s ability in doing the daily tasks. The survey will be taken one day before and one day after the intervention.

### Sample size calculation

The sample size is calculated using Power and Sample Size (PS) software 3.1.2 version [24]. The difference between the mean values of the intervention and control groups, and the standard deviation (post-massage) of SP levels were used as parameters for sample size calculation. Since there is no previous finding of the effect of TMM on substance P, we chose the closest related result based on traditional Thai massage on LBP patients reported by MacKawan et al. [12]. Their study reported that the mean levels of SP in the intervention group and control group are 50.43 pg/mL; 56.27 pg/mL, respectively (the difference in the mean values between the experimental and control groups is 5.84 pg/mL). Their findings also showed that the response within each subject group was normally distributed, with the highest recorded standard deviation being 8.3. The Type I error probability associated with this test of the null hypothesis is 0.05. A sample of 33 experimental subjects and 33 control subjects is therefore required to reject the null hypothesis that the population means of the experimental and control groups are equal, with a probability (power) of 0.8.

### Data analysis plan

Data from participants will be entered into a computerised database and analysed using SPSS software version 20.0. The mean, standard deviation and range will be calculated for each variable. Data will be checked for a normal distribution in terms of skewness and kurtosis, normality test, univariate outliers and missing data. Data will be presented in table and line graphs. The paired *t*-test will be used to measure the differences pre- and post-intervention within and between groups for every outcome measure. A *p*-value of less than 0.05 will be used to show that the result is statistically significant.

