**Methods:**

A non-blinded, randomised controlled trial will be conducted. A total of sixty-six patients who fulfil the inclusion criteria will be recruited. The participants will be randomly allocated into intervention (traditional Malay massage) and control (relaxation position) groups. Blood and saliva samples will be collected before and immediately after intervention. All collected samples will be analysed. The primary outcomes are the changes in the level of substance P in both saliva and blood samples between both groups. The secondary outcomes include the levels of inflammatory mediators [i.e. TNF-α, IL-1β, IL-8, monocyte chemotactic protein-1, IL-6 and IL-10, and the soluble form of the intercellular adhesion molecule], the pain intensity as measured by a visual analogous scale and functional outcomes using the Roland-Morris Disability Questionnaire.

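### The between-arm t-test uses no baseline covariate although every outcome has a baseline value; ANCOVA would gain about 2 to 17 points of power, depending on a pre-post correlation the plan does not give

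*Protocol article*

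**What the plan says.** All references are to the protocol article.

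- **Abstract, Methods:** "Blood and saliva samples will be collected before and immediately after intervention".
- **Outcome measures:** "The primary outcome measure for this study is the difference in the level of SP in blood and saliva samples pre- and post-intervention". The secondary outcomes are seven inflammatory mediators in both fluids, VAS and RMDQ.
- **Instruments:** "Patients will be asked to rate their pain level using the VAS pre- and post- intervention". RMDQ is completed the day before and the day after the session.
- **Data analysis plan:** the only inferential method is a paired t-test: "test will be used to measure the differences pre- and post-intervention within and between groups for every outcome measure". The significance threshold is "A *p*-value of less than 0.05". No covariate or adjusted model is named.
- **Sample size calculation:** this compares mean substance P (SP) between arms using a post-massage SD of 8.3. It states that "the difference in the mean values between the experimental and control groups is 5.84 pg/mL", and "The Type I error probability associated with this test of the null hypothesis is 0.05". It arrives at 33 per arm "with a probability (power) of 0.8".

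**The concern.** Each participant's own pre-session value is available for every outcome, but the planned test uses it only by subtraction. Subtraction fixes the slope of post on pre at 1. When pre and post variances are equal, the actual slope is the pre-post correlation rho, which is below 1 for any measurement with biological or assay noise. A change score therefore takes away too much of the baseline and adds noise to the between-arm comparison. ANCOVA estimates the slope instead.

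Two things are at stake. One is power and precision for the primary SP comparison. The other is how the estimate behaves when arms of 33, formed by simple random allocation, happen to differ at baseline.

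**Working it through.** **Inputs.** From Sample size calculation: difference d = 56.27 - 50.43 = 5.84 pg/mL, SD s = 8.3 (post-massage level), n = 33 per arm, alpha 0.05. Sidedness is not stated. Two-sided is inferred, because the two-sided t calculation returns 33 while a one-sided calculation returns about 25. The article gives neither rho nor an SD of change, so rho is varied from 0.3 to 0.7 and pre and post SDs are taken as equal. Both are assumptions.

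**Step 1: reproduce the plan's figure.** The noncentrality is d / (s·√(2/33)) = 5.84 / (8.3 × 0.2462) = 5.84 / 2.043 = 2.858. On 64 df the two-sided power is 80.4%; with 32 per arm it is 79.1%. The stated 33 per arm reproduces, as a comparison of post-massage means.

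**Step 2: change score against ANCOVA.**

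- SD of change = s·√(2(1-rho)), 64 df.
- Residual SD for ANCOVA = s·√(1-rho²), 63 df, with variance inflated by 1 + 1/62 for estimating the slope.
- Before that small inflation, the variance ratio of ANCOVA to change score is (1-rho²) / (2(1-rho)) = (1+rho)/2.

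| rho | SD change | SD ANCOVA | Power, change | Power, ANCOVA | Gain (points) |
|---|---|---|---|---|---|
| 0.3 | 9.82 | 7.92 | 66.2% | 83.3% | 17 |
| 0.4 | 9.09 | 7.61 | 72.9% | 86.1% | 13 |
| 0.5 | 8.30 | 7.19 | 80.4% | 89.7% | 9 |
| 0.6 | 7.42 | 6.64 | 88.2% | 93.7% | 5 |
| 0.7 | 6.43 | 5.93 | 95.3% | 97.4% | 2 |

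At rho 0.5 the SD of change equals 8.3, so the change-score test has exactly the planned power. It falls below 80% only for smaller rho.

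**Step 3: the other reading, post values only.** Power is then 80.4% whatever rho is. Against the ANCOVA column the gain is 83.3 - 80.4 = 2.9 points at rho 0.3, 89.7 - 80.4 = 9.3 at 0.5, and 97.4 - 80.4 = 17.0 at 0.7. The size of the gain runs the opposite way to Step 2.

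**Step 4: sensitivity to equal SDs.** With post SD 8.3 and pre SD p, the SD of change is √(8.3² + p² - 2·rho·8.3·p). ANCOVA power does not depend on p.

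- p 25% smaller (6.225): the SD of change is 8.75 at rho 0.3 and 7.48 at 0.5. Power is 76% against 83%, and 88% against 90%.
- p 25% larger (10.375): the SD of change is 11.17 and 9.51. Power is 55% against 83%, and 69% against 90%.

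**Step 5: chance baseline imbalance.** Let D be the baseline mean difference between arms. Given D, the expected change-score estimate is off by rho·D - D = -(1-rho)D, which is -0.7D, -0.5D and -0.3D at rho 0.3, 0.5 and 0.7. If the baseline SD is also 8.3, the standard error of D is 2.04 pg/mL. A one-standard-error imbalance at rho 0.5 then shifts the estimate by about 0.5 × 2.04 = 1.0 pg/mL, in the direction opposite to the imbalance.

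**The case against.** The strongest reply has five parts.

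1. **A t-test on change is valid and matches the endpoint as defined.** This stands. Over randomisation the change-score comparison is unbiased, so the point is about efficiency and is not the correction of an error.

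2. **The size is not established by the document.** This also stands. A reader might infer that the plan loses 17 points of power. That figure needs rho 0.3 and equal SDs, and nothing in the article makes 0.3 likelier than 0.7 for samples taken on either side of a 30-minute session.

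3. **The change-score test is itself a reading.** The sentence says paired, between groups as well as within. A paired test does not apply to two independent arms, and an independent t-test on changes is never named. The Outcome measures section supports the change-score reading; the sample size calculation points to post values. The ambiguity is real, but under either reading ANCOVA gains power across the range examined.

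4. **The extension to secondary outcomes is unquantified.** Correct. An effect size and SD are given only for SP. VAS has an entry threshold of 4, which makes equal pre and post variance doubtful. The method carries over to those outcomes, but the power figures do not.

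5. **A condensed article may leave such detail to an analysis plan.** This does not stand here, because the article states a method and applies it to every outcome.

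**Conclusion.** The point holds as an improvement in efficiency that costs nothing in data. For SP, ANCOVA gains about 17 to 2 points of power over a change-score test as rho goes from 0.3 to 0.7, or about 3 to 17 points over a post-only test across the same range. These figures rest on the plan's 5.84 and 8.3, a two-sided 0.05, an assumed rho and, for the change-score comparison, equal pre and post SDs. The direction is secure; the size is not.

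Two stronger readings are not supported. First, the trial is not shown to be underpowered: with equal SDs, the change-score test meets the stated 80% once rho reaches about 0.5, and the shortfall below that depends on a correlation the article does not report. Second, a reader might infer that a chance baseline imbalance passes whole into the result. It does not. Subtraction removes all of the baseline and so over-corrects, leaving -(1-rho)D with the opposite sign, and only conditionally on the imbalance that occurred.

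**What to change.** In the Data analysis plan, replace the between-group use of the t-test with a sentence such as:

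> The between-group effect on each outcome (primary: SP) will be estimated by a linear model of the post-intervention value on treatment arm and the participant's own pre-intervention value (ANCOVA), reporting the adjusted mean difference with its 95% CI and p-value.

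Keep paired t-tests, if wanted, only to describe change within each arm. This also removes the uncertainty about which between-arm test is meant.

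The cost is one sentence and one degree of freedom. The baseline values are already collected and ANCOVA is available in the SPSS version named. No participants, samples or procedures are added, and under the plan's inputs 33 per arm still gives at least 80% power at every correlation examined.

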## Methods

### Study design

A non-blinded, 2-arm randomized controlled trial will be conducted. A total of 66 eligible participants will be randomly assigned into two groups: (i) TMM or (ii) control groups, using a simple random sampling method. Random allocation to either the intervention or control group is achieved by sequentially numbered, sealed opaque envelopes containing the group allocation, which will be determined by a computer-generated random number. A research assistant with no direct contact with the participants will be responsible for generating the random numbers and preparing the envelopes. Ethical approval has been obtained from the UiTM Research Ethics Committee [600-RMI(5/1/6)].

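### The only test named for comparing the two randomised arms is a paired t-test, although the arms are unmatched and the sample size assumes independent groups

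*Protocol article*

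**What the plan says.** - **Test (Data analysis plan).** One inferential test is named for everything: the paired t-test "will be used to measure the differences pre- and post-intervention within and between groups for every outcome measure". No independent-samples test, ANCOVA or mixed model appears anywhere in the article.
- **Design (Study design).** "A non-blinded, 2-arm randomized controlled trial will be conducted". Participants are individually allocated by sealed envelopes from computer-generated numbers, to "i) TMM or (ii) control groups, using a simple random sampling method". No matching is described.
- **Primary outcome.** The Abstract (Methods) makes it a contrast between arms: "The primary outcomes are the changes in the level of substance P in both saliva and blood samples between both groups". The Outcome measures section words it as "the difference in the level of SP in blood and saliva samples pre- and post-intervention", without naming the arms.
- **Sample size (Sample size calculation).** The trial is sized to "reject the null hypothesis that the population means of the experimental and control groups are equal". The inputs are a difference of 5.84 pg/mL, a within-group post-massage SD of 8.3, alpha 0.05 and power 0.8, giving 33 per arm.

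**The concern.** A paired t-test analyses differences within linked pairs. Before and after values from one person are such a pair. A massage participant and a control participant in a parallel-group trial are not. Using the paired test between arms therefore needs an arbitrary pairing and equal numbers in each arm.

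Two outcomes are possible if the plan is followed:

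1. The analyst lines the arms up in some order. The p-value then depends on that order, and unequal arms force participants to be dropped.
2. The analyst runs only the paired tests that make sense, before versus after within each arm. That discards the randomised comparison and invites the inference that massage worked because its arm reached significance and the control arm did not.

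The sentence covers every outcome measure, so the primary and all secondary comparisons are affected.

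**Working it through.** **1. Which test does the sample size assume?** Inputs from the Sample size calculation: difference 56.27 − 50.43 = 5.84; SD 8.3; alpha 0.05 (sidedness is not stated; two-sided is assumed because it reproduces the plan); power 0.80.

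- Normal approximation, independent groups: n per arm = 2 × (1.960 + 0.842)² × (8.3/5.84)² = 31.7, so 32.
- Exact noncentral t at 33 per arm: noncentrality 5.84 / (8.3 × √(2/33)) = 2.858 on 64 df gives power 0.804. At 32 per arm it is 0.791. The plan's 33 is reproduced exactly.
- Independent groups, one-sided: 25 per arm. Does not fit.
- Paired t-test with 8.3 as the SD of differences: 18 pairs. Does not fit.

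The plan is sized for an independent two-group test and names a paired one.

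**2. Error rate and power under arbitrary pairing of 33 with 33.** With unrelated pairs the SD of differences is 8.3 × √2 = 11.74, so the noncentrality is again 2.858. The df fall from 64 to 32 and the critical value rises from 1.998 to 2.037. Power is 0.791 against 0.804. Simulated type I error is 0.050 paired and 0.049 unpaired (50,000 runs).

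**3. Dependence of p on the pairing.** With equal SDs, paired t ≈ unpaired t / √(1 − r), where r is the chance correlation the pairing creates. Over random pairings r has mean 0 and SD 1/√32 = 0.177, so its central 95% is about ±0.346. Take a dataset with unpaired p = 0.050 (t = 1.998):

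| r | paired t (32 df) | p |
|---|---|---|
| +0.346 | 2.471 | 0.019 |
| 0 | 1.998 | 0.054 |
| −0.346 | 1.722 | 0.095 |

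Paired p is below 0.05 when r > 1 − (1.998/2.037)² = 0.038, which happens in about 41% of pairings. Simulation with 20,000 random pairings agrees (0.019 to 0.095, 41%). Away from the borderline the effect is milder: a dataset with unpaired p = 0.013 gave paired p from 0.004 to 0.034.

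**4. Equal arms.** If the 66 allocations are unrestricted 1:1 draws, P(33/33) = C(66,33)/2⁶⁶ = 0.098. The expected difference in arm size is 66 × 0.0978 = 6.46. About 90% of the time the arms would differ, and about 6 participants on average would have no partner.

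**5. Within-arm tests only.** Suppose both arms have the same true standardised change d, so there is no treatment effect. With 33 per arm and within-arm power P, the chance that exactly one arm is significant is 2P(1 − P):

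| d | P | 2P(1 − P) |
|---|---|---|
| 0.3 | 0.387 | 0.474 |
| 0.4 | 0.606 | 0.478 |
| 0.5 | 0.795 | 0.326 |

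The values of d are illustrative; the article gives none.

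**6. Power after correction, 33 per arm.** An independent t-test on post-intervention values has power 0.804. For the other options the pre/post correlation ρ is needed; the article does not give it. Assuming SD 8.3 at both times:

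| ρ | t-test on change, SD 8.3√(2(1−ρ)) | ANCOVA, SD 8.3√(1−ρ²) |
|---|---|---|
| 0.3 | 0.66 | about 0.84 |
| 0.5 | 0.80 | about 0.90 |
| 0.7 | 0.95 | about 0.98 |

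**The case against.** The strongest reply is that this is a drafting slip. One sentence of a condensed article covers two kinds of comparison, the paired test fits the before/after part, and the sample size section shows that an independent comparison was in mind. That may well be what was intended. But the sentence assigns the paired test to the between-group comparison, and no other test is named to carry it. This is a test stated wrongly, not a detail left to a document we have not seen, and a slip in the primary test still has to be corrected.

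Three points about size are fair and stand:

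- Pairing fixed without regard to outcome does not inflate type I error, and the loss of df costs only about 1.3 points of power.
- The 0.019 to 0.095 range is for a borderline dataset; at p = 0.013 almost no pairing would change the conclusion.
- The 9.8% figure assumes unrestricted allocation. Envelopes prepared as 33 and 33 would also fit the text and give equal arms at the start. Even then, one missing sample in one arm would unbalance them.

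It is also fair that the error itself requires only an independent-samples test. ANCOVA is an improvement on that minimum.

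**Conclusion.** The concern holds: the between-group test is wrong as written. The article pairs participants who are not matched, names no other test for its primary contrast, and contradicts its own sample size, which is reproduced only by the independent two-group test.

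The seriousness does not rest on a distorted error rate. It rests on the primary analysis having no usable definition: it is order-dependent, impossible with unequal arms, or replaced by within-arm tests that do not compare the arms. The conclusion itself follows from the text alone. The figures on its size assume normal data, a two-sided 5% level and, for the arm-size figure, unrestricted randomisation. It must be fixed before analysis.

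**What to change.** In the Data analysis plan, restrict the paired t-test to describing change within each arm, and add a sentence for the between-arm comparison. For example: *Each outcome will be compared between arms by ANCOVA of the post-intervention value on treatment group and baseline value, reporting the adjusted mean difference with its 95% confidence interval.* The minimum correction is an independent-samples t-test on the change from baseline. The first is preferable: it uses baseline data already being collected and, under the assumptions above, has more power than the change-score test at each correlation considered. If the change score is kept, note that its power falls below 0.80 when the pre/post correlation is under 0.5.

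The cost is one or two sentences. Software, data, procedures and the 66 participants stay as planned.

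### Within-arm pre/post tests share one p<0.05 rule with the randomised comparison, and Methods words the primary outcome as a pre/post difference, so the deciding contrast is not fixed

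*Protocol article*

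**What the plan says.** Four places in the protocol article bear on which contrast decides the trial.

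- **Data analysis plan.** A paired t-test "will be used to measure the differences pre- and post-intervention within and between groups for every outcome measure". One threshold follows for all of these tests: a p-"value of less than 0.05 will be used to show that the result is statistically significant". No test is ranked above another.
- **Outcome measures (Methods).** "The primary outcome measure for this study is the difference in the level of SP in blood and saliva samples pre- and post-intervention". The sentence mentions no comparison between arms.
- **Abstract, Methods.** "The primary outcomes are the changes in the level of substance P in both saliva and blood samples between both groups". Here the contrast is between arms.
- **Sample size calculation.** The planning effect is a between-arm one: "the difference in the mean values between the experimental and control groups is 5.84 pg/mL". The null hypothesis is equality of the two arms' population means, and alpha is attached to it: "The Type I error probability associated with this test of the null hypothesis is 0.05".

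**The concern.** The control arm is there to remove whatever would have changed without massage. A pre/post test inside the TMM arm does not use it. Such a test responds to a massage effect and equally to any change that controls would show too.

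The article itself gives reasons to expect shared change:

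- Controls spend 30 minutes in a relaxation position, and the Background and Discussion list relaxation among the effects of massage.
- Entry requires a VAS score of at least 4, so VAS may fall on re-rating through regression to the mean.
- The trial is not blinded.
- For blood, saliva and VAS the change spans the session. The Roland-Morris questionnaire is taken one day before and one day after, so shared change there covers a longer interval.

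The Methods wording of the primary outcome and the single threshold together leave room for a significant fall in the TMM arm to be reported as the primary result when the arms do not differ. The Discussion expects the trial to support prescribing TMM, and that conclusion should rest on the randomised contrast.

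The choice of t-test between arms is a related but separate matter. Correcting it would leave the within-arm tests under the same rule.

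**Working it through.** **1. The plan's own figure.** Inputs from the Sample size calculation: difference 5.84 pg/mL; SD 8.3 ("with the highest recorded standard deviation being 8.3"); alpha 0.05, taken as two-sided; "with a probability (power) of 0.8"; 33 per arm.

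- Normal approximation: n = 2(1.960 + 0.842)² × (8.3/5.84)² = 31.7, so 32 per arm.
- Exact noncentral t for two independent samples at n = 33: noncentrality = 5.84 / (8.3 × √(2/33)) = 2.858 on 64 df, power 0.804. At n = 32 the power is 0.791.

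The stated 33 per arm is exact, and it is the size for a between-arm comparison of means.

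**2. The within-arm test when massage does nothing.** Let both arms have the same mean change, equal to d standard deviations of the change score. For a two-sided paired t-test with n = 33, the noncentrality is d√33 = 5.745d on 32 df, with critical value 2.037. The between-arm column is a simulation of 100,000 trials per row, using an independent-samples t-test on change scores.

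| Shared shift d (assumed) | Noncentrality | TMM within-arm p<0.05 | Between-arm p<0.05 |
|---|---|---|---|
| 0 | 0 | 0.050 | 0.050 |
| 0.2 | 1.149 | 0.200 | 0.049 |
| 0.35 | 2.011 | 0.496 | 0.049 |
| 0.5 | 2.872 | 0.795 | 0.050 |

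The simulation gave 0.050, 0.201, 0.497 and 0.797 for the within-arm column, in agreement with the formula.

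**3. The same on the SP scale.** The 8.3 is a post-massage SD, not an SD of change. If the SD is the same before and after and the pre/post correlation is ρ, the SD of change is 8.3 × √(2(1 − ρ)). The article does not give ρ, so a range is shown.

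| ρ (assumed) | SD of change | Shared change 1 pg/mL | Shared change 3 pg/mL |
|---|---|---|---|
| 0.3 | 9.82 | 0.088 | 0.398 |
| 0.5 | 8.30 | 0.103 | 0.522 |
| 0.7 | 6.43 | 0.140 | 0.739 |

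Entries are the probability that the TMM within-arm test is significant with no massage effect.

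**4. The named test.** A paired t-test needs paired observations. Pre and post values in one patient are paired; patients in different arms are independent. The named test therefore fits only the within-arm contrast, and the 5% benchmark in step 2 requires a method for independent groups.

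**The case against.** The strongest reply is that the randomised comparison is already planned, powered and named. The Abstract states it, the Data analysis plan includes a between-group test, and the Sample size calculation ties alpha, power and the 33 per arm to equality of the two arm means. The Outcome measures sentence can be read as naming the per-patient variable, with the Abstract supplying the contrast. All of this stands, and it shows what the authors most likely intend. It does not remove the problem: nothing in Methods links the change score to a between-arm comparison, and the Data analysis plan puts both kinds of test under one rule.

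A second reply is that ranking tests is commonly left to a statistical analysis plan, which is not shown. That would answer a mere omission. Here the article prescribes within-arm tests for every outcome and words its primary outcome in two ways.

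Third, the size depends on the assumed shift. That is correct. With no shared shift a single within-arm test errs 5% of the time, as it should.

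A reader might infer more: that the plan makes a within-arm p-value proof of a TMM effect, or that significance in TMM but not in control would count as success. The second rule would err 16%, 25% and 16% of the time at shifts of 0.2, 0.35 and 0.5 SD, from p(1 − p). The documents support neither inference. No section says that a within-arm result establishes an effect, and the TMM-only rule appears nowhere.

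**Conclusion.** The point holds as a conflict in the text together with a rule that does not separate the two kinds of test. Outcome measures and the Data analysis plan leave room for a pre/post reading of the primary result; the Abstract and the Sample size calculation rest on the randomised contrast.

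If a within-arm result were taken as evidence, the chance of a significant TMM result without a massage effect would run from 5% with no shared shift to about 80% at 0.5 SD of the change score, against 5% for a valid between-arm test. These figures assume 33 analysed per arm, normal change scores and the stated shifts. The article gives no shared shift, no SD of change and no pre/post correlation. The 5% is per test; SP in blood and SP in saliva are two tests.

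The documents do not show that the authors intend to claim an effect from a within-arm test, and the stated sample size is correct for the between-arm comparison.

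**What to change.** - **Outcome measures:** define the primary outcome as the TMM-minus-control difference in pre-to-post SP change, in line with the Abstract and the Sample size calculation.
- **Data analysis plan:** state that any claim of a TMM effect, for any outcome, rests only on the between-arm difference with its 95% confidence interval. Estimate it by a method for independent groups: ANCOVA with the baseline value as covariate, or an independent-samples t-test on change scores.
- **Within-arm changes:** report means and SDs descriptively, not as evidence of a TMM effect.

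The cost is a few sentences, with no added patients, samples or procedures. The 33 per arm stays, since it was computed for the between-arm comparison (power 0.804 at an SD of 8.3). One point bears on the choice of method. Change scores keep that power only if their SD is no more than 8.3, which means ρ of at least 0.5 under the formula in step 3. ANCOVA has a residual SD of about 8.3 × √(1 − ρ²), which never exceeds 8.3, so it is the safer choice while ρ is unknown. The only loss is the use of within-arm p-values as evidence, and they do not test the treatment.
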